### Randomization

Municipality districts are randomized so that all patients living within the same municipality district receive either telehealthcare in addition to usual care or just usual care. The randomization will not be undertaken until after all general practitioners have sent their lists of patients eligible for inclusion from their practice, and after all patients have given written consent to participation and completed baseline physical measurements and questionnaires. There will be 13 individual randomization ‘draws’ from the 26 matched municipality districts. The randomization will be done by the sealed envelope method by a person not affiliated with the trial. The randomization event will be videotaped.

### Compared alternatives

#### Usual practice

Danish healthcare is tax-funded and almost entirely publicly provided, which means that all Danish citizens and legal immigrants can access the full breadth of acute and planned medical care without any out-of-pocket payments. Five Danish Regions are responsible for supplying healthcare services to citizens, so hospitals and their staff, as a rule, are publicly owned and operated; primary care is provided via regulated contracts with independent general practitioners. The 98 municipalities in Denmark have a specialized role in rehabilitation and community care where nursing and practical help is required in the patients’ own homes.

In Denmark, usual practice for treating, monitoring, and caring for patients with COPD involves the responsibility of the patient’s general practitioner (treatment and monitoring) and that of the municipalities (practical help and nursing care). COPD patients can make appointments with their general practitioner or practice nurse free of charge in order to get help in managing their COPD. Community-based care and practical help varies across the municipalities. As a rule, community care is provided at regular intervals based on a clinical evaluation of the patients’ needs. But the personnel are not necessarily certified nurses and they are usually not particularly skilled in the handling of COPD and definitely not on a telephone call basis.

Municipality healthcare personnel in the control group will not receive the training described below, and the individual COPD patients will continue their usual treatment and care throughout the study period (12 months).

#### Intervention

The telehealth solution is a tablet (Samsung Galaxy Tab2 (10.1)) that contains information on handling COPD in general and software that automatically instructs the patient in handling COPD during exacerbations. The device can also collect and wirelessly transmit relevant disease-specific data indicative of the patient’s current state of health: blood pressure, pulse, blood oxygen saturation, and weight. This is made possible via an attached Fingertip Pulse Oximeter (Nonin, Onyx II% SpO2, A & D Medical, Tokyo, Japan), a Digital Blood Pressure Monitor (Model UA-767, plus BT-C, Nonin Medical, Minnesota, USA), and a scale (Precision Health Scale, UC-321PBT-C, A & D Medical, Tokyo, Japan). The software was developed by Silverbullit, Aarhus, Denmark (http://opentele.silverbullet.dk). The tablet can be activated and sound an alarm when it is time for taking measurements again. Patients and their relatives can access the data via a web portal (http://www.sundhed.dk).

At the cluster-level, around 100 municipality healthcare personnel (mostly community care nurses) will be responsible for patient care and monitoring in the intervention group. They will be trained by members of the trial administration office. The training consists of two full-day workshop sessions: Session 1 focuses on the technical aspects of the tablet (how to use it) and the physical measurements (how to perform the measurements using the tablet and how to monitor threshold values). Session 2 focuses on general disease awareness and communication with patients.

At the individual level, COPD patients in the intervention group will be contacted by telephone by their municipality no later than 10 days after randomization, and a 45-minute appointment is scheduled for patients who want to receive the tablet at home. For those who wish to receive the tablet at a municipality health center, a 75-minute appointment is scheduled with 3 to 4 patients in each group. A relative is allowed to participate as well. At this appointment, a nurse from the COPD patient’s municipality instructs the patient in the use of the Telekit. The nurse demonstrates how to use the tablet and how to take physical measurements, and the nurse guides the patient through the tablet manual before letting the patient try the tablet him or herself. Patients will be asked to measure their vital signs daily during the first two weeks (both weekdays and weekends) and 1 to 2 times weekly after the two first weeks (the specific days are agreed upon and programmed into the tablet by the nurse). The nurse also describes the monitoring procedure and gives the patient contact information to the community nurse. Finally, a 45-minute follow-up visit is scheduled 3 to 4 weeks after the first appointment to check if the patient uses the device appropriately and if the threshold values of the physical measurements need to be adjusted.

The patient’s residing municipality is responsible for monitoring the data obtained with the telehealth device. Exemptions are COPD patients receiving oxygen therapy and COPD patients with open hospital admissions. Such patients are monitored at a specialized hospital lung ward. Patients are monitored asynchronously by a nurse on a daily basis or no later than a weekday after each measurement. Measurements are classified with either a green, yellow or red code. A green code is given if no threshold values are exceeded. If the code given is yellow (that is, one or more values exceed the threshold values) or red (that is, one or more values exceed the threshold values and have not previously been recorded), a nurse will decide which response is necessary. The following options are available: The patient may be instructed to commence self-treatment by the tablet or the nurse can contact the patient by telephone to assess the situation, and pending the patient’s acceptance, the patient’s general practitioner can be contacted directly. Finally, an ambulance can be dispatched by the nurse.

### Outcomes

The primary outcome for theme 1 (effectiveness) is the change in health-related quality of life (SF-36) at the individual level from baseline to follow-up at 12 months. This study hypothesizes that adding telehealthcare to usual care will lead to a significantly higher health-related quality of life for the included participants.

Secondary outcomes for theme 1 are changes in mortality and physiological parameters (diastolic blood pressure, systolic blood pressure, pulse, oxygen saturation, and weight) from baseline to the follow-up at 12 months. The clinical impact of telehealthcare is assessed as being beneficial if there is no changes in mortality and if pulse and blood pressure are lowered and oxygen saturation is raised.

The primary outcome for theme 2 is the incremental cost-effectiveness ratio (ICER) measured as the cost per quality adjusted life years (QALY) gained from baseline to follow-up at 12 months. It is expected that telehealthcare will increase the patients’ QALY compared with usual practice, since no difference in mortality and a higher health-related quality of life are expected. Furthermore, it is hoped that telehealthcare will reduce the number of admissions and readmissions to hospitals as well as the number of outpatient visits by 30%, which will reduce hospital costs [13,19]. However, these savings could be offset by other costs such as more visits to general practitioners, community care, medicine consumption or the cost of implementing telehealthcare.

Outcomes will be measured at both the individual level and at cluster level.

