### Sample size

The sample size calculation for theme 1 was performed in STATA v12. Based on a recent Norwegian study, it is hypothesized that the COPD patients eligible for inclusion have a mean SF-36 Physical Component Summary (PCS) score of 38 at baseline with a standard deviation of 10 [20]. The average cluster size is hypothesized to be 50 with a coefficient of variation of 0.5. Conservative estimates are applied for the minimal clinically important difference (change equal to 5) and intracluster correlation ((ICC) equal to 0.05). With a power of 80% and a two-sided *P* value of <0.05, the required sample size is estimated to be 350 participants and at least seven clusters in each arm.

With an expected loss-to-follow-up of 10%, the total required sample size is estimated to be around 800 participants.

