### Statistical methods

Statistical analysis will be performed with an intention-to-treat principle and be presented according to the extensions of the CONSORT statement for cluster-randomized clinical trials [21]. Missing data (other than censoring) will be evaluated to assess the occurrence of specific missing data patterns and, if necessary, Multiple Imputation will be used and observations will be reported according to epidemiological guidelines [22]. If appropriate, an adjustment for differences in patient and/or cluster baseline characteristics (for example, age, gender, co-morbidities, educational level, marital status, proportion of COPD patients) in both the telehealthcare group and in the usual care group will be made.

To assess effectiveness in theme 1, a comparison of differences in mean SF-36 scores, mortality and physical measurements from baseline to 12 months after randomization between the telehealthcare group and the control group will be analyzed using statistical methods suitable for cluster-randomized trials, for example, multilevel modeling.

To assess the cost-effectiveness in theme 2, a point estimate of the ICER will be calculated after 12 months. The ICER is defined as the difference in arithmetic mean costs between the telehealthcare intervention and usual care divided by the difference in arithmetic mean effectiveness between the same intervention groups as shown in Equation (1).

Equation 1 shows how the incremental cost-effectiveness ratio (ICER) is calculated:

(1)$$\mathrm{ICER}=\frac{C_{\text{Telehealthcare}}-C_{\text{Usual}\;\text{care}}}{E_{\text{Telehealthcare}}-E_{\mathrm{Usual}\;\text{care}}}$$

The incremental effectiveness for the cost-effectiveness calculation is estimated from the utility scores from the EQ5D-3 L health-related quality of life questionnaire with Danish societal weights [23]. From these, QALYs can be calculated by linear interpolation of utility scores between baseline and the follow-up at 12 months by measuring the area under this curve.

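### The benefit rule for the secondary outcomes asks for unchanged mortality without a direction: fewer deaths do not meet it as worded, and on a significance reading a material excess could

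*Protocol article*

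**What the plan says.** The Outcomes section of the protocol article sets out the theme 1 secondary outcomes: "Secondary outcomes for theme 1 are changes in mortality and physiological parameters", the latter being blood pressure, pulse, oxygen saturation and weight. It then gives a rule for reading them together. Clinical impact will be "assessed as being beneficial if there is no changes in mortality and if pulse and blood pressure are lowered and oxygen saturation is raised".

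In the next paragraph, on theme 2, the article explains why more quality-adjusted life years are expected: "since no difference in mortality and a higher health-related quality of life are expected". That is an expectation and not a second rule.

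Under Statistical methods, the between-arm differences in SF-36, mortality and physical measurements "will be analyzed using statistical methods suitable for cluster-randomized trials, for example, multilevel modeling". The article's only significance criterion, a "two-sided *P* value of <0.05", stands in the Sample size section, which concerns the SF-36 physical component score.

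**The concern.** The rule joins several conditions with *and*. Pulse and blood pressure must fall and saturation must rise, but mortality must merely not change. Two difficulties follow.

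- **A reduction.** Fewer deaths is a change, so the most favourable mortality result does not satisfy the condition that leads to a finding of benefit.
- **An increase.** Some method must decide whether mortality has changed. If that method is a non-significant test, the condition is easiest to meet when the data say least, and absence of evidence is reported as evidence of no harm.

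What is at stake is the sentence that the trial report may write about clinical impact. According to the Background and the Discussion, the results feed a decision on a national telehealthcare standard. A statement of benefit with unchanged mortality would accompany them even if the interval allowed a sizeable excess of deaths.

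**Working it through.** **1. The plan's own figure.** The article states a sample size for SF-36 only. Inputs (Sample size section): difference 5, a mean "score of 38 at baseline with a standard deviation of 10", two-sided 0.05, power 80%, mean cluster size 50, coefficient of variation 0.5, ICC 0.05.

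- Per arm without clustering: 2 × (1.960 + 0.842)² × 10² / 5² = 62.8.
- Design effect: 1 + [(0.5² + 1) × 50 − 1] × 0.05 = 4.075.
- 62.8 × 4.075 = 256 per arm, or 256 / 50 = 5.12 clusters. One added cluster as a small-number correction gives 6.12, rounded up to 7. Then 7 × 50 = 350 per arm, as stated.
- 10% loss: 700 / 0.9 = 778, consistent with the stated figure of around 800.

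The figure reproduces, but it contains nothing about mortality.

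**2. What could unchanged mortality mean?**

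- *Identical death counts.* With 400 to 600 independent patients per arm and assumed mortality of 3% to 10%, two truly equal arms would show equal counts only about 4% to 8% of the time. This reading is unworkable.
- *No significant difference at two-sided 0.05.* This is workable, and it fits the planned between-arm comparison. The article does not state it.

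**3. Precision on the second reading.** From the article: 1,200 expected participants, taken as 600 per arm; 26 districts, hence 24 degrees of freedom if the pairing is ignored; coefficient of variation 0.5. Assumed, because the article gives neither: 12-month mortality p of 5% to 10% and a mortality ICC of 0 to 0.01.

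- Mean cluster size: 1,200 / 26 = 46.15.
- Design effect at ICC 0.01: 1 + (1.25 × 46.15 − 1) × 0.01 = 1.57.
- Half-width = t(24; 0.975) × √[2p(1 − p) / 600 × design effect], with t = 2.064.

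| Assumed p | ICC 0 | ICC 0.01 |
|---|---|---|
| 5% | 2.6 points (52% of p) | 3.3 points (65% of p) |
| 10% | 3.6 points (36% of p) | 4.5 points (45% of p) |

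For example, at p = 5% and ICC 0: √(2 × 0.05 × 0.95 / 600) = 0.01258, and 2.064 × 0.01258 = 0.026.

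**4. Cross-check with a pooled z-test on the effective sample size.** Control mortality is assumed to be 5%.

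| Patients | Mortality ICC | Highest telehealthcare rate still non-significant | Chance of missing a true 50% relative increase |
|---|---|---|---|
| 1,200 | 0 | 7.8% | 57% |
| 1,200 | 0.01 | 8.6% | 70% |
| 800 | 0 | 8.5% | 69% |
| 800 | 0.01 | 9.2% | 76% |

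If the SF-36 ICC of 0.05 were borrowed for mortality, the chance of missing it would be 85% at 1,200 patients and 86% at 800.

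**The case against.** The strongest reply is that the sentence says *if*, not *only if*. It describes a sufficient condition. Since the following paragraph expects no mortality difference, it probably describes the expected scenario: survival unchanged and physiology better. A reader might infer that the plan would deny benefit because fewer patients died. The text does not go that far. A reduction is left outside the rule and is not declared a failure. What stands is the narrower point that a reduction does not meet the condition as written. On the significance reading this applies only to a significant reduction, which on the half-widths above means a relative fall of roughly 36% to 65%.

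A reader might also infer that the plan equates a non-significant result with unchanged mortality. It never says so, and read literally any increase would fail too. The second difficulty is therefore conditional on how the rule is applied.

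Three further objections are sound. A test or margin may properly be left to an analysis plan that is not shown, so its absence alone is no fault. Sizing the trial on SF-36 and not on mortality is no fault either, because mortality is a secondary outcome. The death rates and the mortality ICC are assumptions.

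These objections do not supply a direction, however. The same sentence gives one for pulse, blood pressure and saturation, and an analysis plan that treated fewer deaths as favourable would have to depart from the protocol's wording.

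**Conclusion.** The point holds in a limited form. From the text alone, the mortality condition has no direction, so a reduction in deaths does not satisfy it. Under the practicable but unstated significance reading, a material excess could satisfy it. With 600 per arm, assumed mortality of 5% to 10% and an assumed ICC of 0 to 0.01, the 95% half-width is about 2.6 to 4.5 percentage points, or roughly 36% to 65% of the assumed rate. These figures show how little a non-significant mortality result would establish; they do not show an error in the sample size.

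The importance is minor to moderate. A reader might take the rule to be the trial's success criterion, but the documents do not support that. Theme 1 is judged on SF-36 and theme 2 on the incremental cost-effectiveness ratio, and the Discussion ties national adoption to cost-effectiveness. None of these changes, and neither does the sample size.

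**What to change.** Reword the mortality condition as no increase in mortality, and say that a reduction counts in favour. Report the between-arm mortality difference with its 95% confidence interval from the cluster-aware analysis already planned, and state that a non-significant difference is not evidence of no harm. Then choose one of two courses:

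- claim no excess mortality only if the upper confidence limit lies below a margin that the sponsor fixes before data are seen; or
- take mortality out of the benefit rule, report the interval, and state that excess mortality is not excluded.

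The cost is a few lines in the protocol or analysis plan. No extra patients or data are needed. The downside is a slightly less favourable mortality statement.

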### Sample size

The sample size calculation for theme 1 was performed in STATA v12. Based on a recent Norwegian study, it is hypothesized that the COPD patients eligible for inclusion have a mean SF-36 Physical Component Summary (PCS) score of 38 at baseline with a standard deviation of 10 [20]. The average cluster size is hypothesized to be 50 with a coefficient of variation of 0.5. Conservative estimates are applied for the minimal clinically important difference (change equal to 5) and intracluster correlation ((ICC) equal to 0.05). With a power of 80% and a two-sided *P* value of <0.05, the required sample size is estimated to be 350 participants and at least seven clusters in each arm.

With an expected loss-to-follow-up of 10%, the total required sample size is estimated to be around 800 participants.

### Statistical methods

Statistical analysis will be performed with an intention-to-treat principle and be presented according to the extensions of the CONSORT statement for cluster-randomized clinical trials [21]. Missing data (other than censoring) will be evaluated to assess the occurrence of specific missing data patterns and, if necessary, Multiple Imputation will be used and observations will be reported according to epidemiological guidelines [22]. If appropriate, an adjustment for differences in patient and/or cluster baseline characteristics (for example, age, gender, co-morbidities, educational level, marital status, proportion of COPD patients) in both the telehealthcare group and in the usual care group will be made.

To assess effectiveness in theme 1, a comparison of differences in mean SF-36 scores, mortality and physical measurements from baseline to 12 months after randomization between the telehealthcare group and the control group will be analyzed using statistical methods suitable for cluster-randomized trials, for example, multilevel modeling.

To assess the cost-effectiveness in theme 2, a point estimate of the ICER will be calculated after 12 months. The ICER is defined as the difference in arithmetic mean costs between the telehealthcare intervention and usual care divided by the difference in arithmetic mean effectiveness between the same intervention groups as shown in Equation (1).

Equation 1 shows how the incremental cost-effectiveness ratio (ICER) is calculated:

(1)$$\mathrm{ICER}=\frac{C_{\text{Telehealthcare}}-C_{\text{Usual}\;\text{care}}}{E_{\text{Telehealthcare}}-E_{\mathrm{Usual}\;\text{care}}}$$

The incremental effectiveness for the cost-effectiveness calculation is estimated from the utility scores from the EQ5D-3 L health-related quality of life questionnaire with Danish societal weights [23]. From these, QALYs can be calculated by linear interpolation of utility scores between baseline and the follow-up at 12 months by measuring the area under this curve.

In calculating the incremental costs, this trial adopts a healthcare sector perspective in the base case analysis, which means that all costs to healthcare providers involved in treating, caring, and monitoring COPD patients are included [24]. Included cost categories are intervention costs, in- and outpatient costs, medication costs, costs from visiting general practitioners, and community care costs (primarily due to home nurse visits in the municipalities). This choice of perspective for the base case analysis means that the calculation of costs per QALY excludes costs incurred by patients and relatives (primarily due to transportation and time) and costs due to productivity loss to society. Excluding cost of productivity loss is normal practice in economic evaluation when conducting cost-utility analysis because of the risk of double counting [24]. To allow for later sensitivity analysis, information on productivity loss is gathered at 12 months by use of the Work Productivity and Activity Impairment questionnaire (WPAI) [25]. The WPAI measures self-reported absence from work, reduction in productivity while at work, and reduction in productivity while doing regular activities (other than work) in order to be able to assess the cost-of-illness to society at follow-up. Costs to patients and relatives are sought estimated from the literature.

Denmark is internationally recognized for having a rigorous registration of data on health activities. All Danish citizens have a social security number, which is a 10-digit unique identity number. All Danish citizens’ contacts with the healthcare sector are registered in various registers with this identification number. Through cross-linking of registers, data may be extracted at the level of the individual to obtain a fairly accurate picture of the individual's consumption of health care resources/services across municipalities, hospitals, and general practitioners.

Three national registers are relevant in the present study: Firstly, *The Danish National Patient Register* contains national patient-level data for all hospital contacts (patient cpr-number, date of beginning/end of contact, diagnoses, treatments, and place of contacts). The register contains data on all inpatient, outpatient, and emergency ward visits in Denmark. Secondly, *The National Health Insurance Service Register* covers all contacts between patients and the primary care sector (general practitioners, physiotherapists, *etcetera*). The health authorities in Denmark use the register for administrative purposes, especially for the settling of accounts. The register contains data on all citizens, providers, and healthcare services reimbursed by the health authorities. Thirdly, *The Register of Medicinal Product Statistics* contains detailed information about the total sales of prescribed medicine in Denmark. Around 30 different items of information are registered every time a medicinal product is sold on prescription.

Finally, data on the use of community care is collected from the individual care systems in the residing municipalities and implementation cost are collected from cost diaries from the trial administration office.

Unit costs will be calculated for each of the resource parameters in order to determine the average costs per patient at baseline and at the 12-month follow-up. Point estimate for the average costs in the telehealthcare group and in the usual care group are then derived from univariate and multivariate analysis.

The cost-effectiveness analysis will be subject to both one-way and probabilistic sensitivity analysis (PSA). This is a standard way of analyzing and presenting results from a cost-effectiveness calculation that allows the recipients of the analysis to get a sense of the impact of different uncertainties in parameter values on the probability that telehealthcare is cost-effective at different levels of willingness to pay for an improvement in QALYs [26,27]. Another trial ambition is to expand the healthcare sector view to include costs incurred by patients and relatives (primarily due to transportation and time) and costs due to productivity loss to society that were excluded in in the base case scenario of total cost per QALY.

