Eligible patients are enrolled by the general practitioners. All general practitioners (supported by their local union) have agreed in advance of the trial to make individual appointments with each eligible patient listed with their practice. Before the appointment, the general practitioner posts a written folder to the patients informing them about the study and their legal rights. The appointment lasts approximately 30 minutes per patient. At the appointment, the general practitioner repeats information about the trial, hands out the same information folder that was sent to the patient before the appointment, takes baseline physical measurements (spirometry, mMRC and CAT scores, weight, pulse and blood pressure), and written informed consent is obtained if the patient accepts trial participation. If the general practitioner has obtained physical measurements less than 30 days before the appointment, these data can be used as baseline physical measurements instead.

The general practitioner sends the signed informed consent forms together with the list of eligible patients and the filled in forms with baseline physical measurements to the trial administration office using the first pre-stamped envelope. The general practitioner also distributes the patient-questionnaire which includes questions about the patients’ baseline health-related quality of life (EQ5D and SF-36) and demographic characteristics (age, gender, education, comorbidities, smoking status, marital and job status). The patient-questionnaire is filled out in the comfort of the patients’ own homes no later than two weeks after their visit to the general practitioner and must be sent to the trial administration office using the second pre-stamped envelope. The trial administration’s telephone number is printed on the questionnaires and patients are invited to contact the office if they need help to answer the questionnaire. Both envelopes are returned to the office before randomization.

Finally, the general practitioners electronically refer patients eligible for inclusion into the trial to the residing municipality where threshold values for body mass index, blood pressure, and blood oxygen saturation are established. These threshold values are individually determined for each patient and will be used in the monitoring of the patients by the municipalities’ community healthcare personnel.

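### The primary SF-36 analysis compares change scores and adjusts for baseline only if differences are seen, where a pre-fixed baseline-adjusted model would be more precise and not open to data-driven choice

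*Protocol article*

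**What the plan says.** The Outcomes section states that the theme 1 primary outcome "is the change in health-related quality of life (SF-36) at the individual level from baseline to follow-up at 12 months". Statistical methods then describes the analysis as "a comparison of differences in mean SF-36 scores, mortality and physical measurements from baseline to 12 months after randomization", compared between arms with "statistical methods suitable for cluster-randomized trials, for example, multilevel modeling".

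The adjustment rule stands in the same section. It reads "If appropriate, an adjustment for differences in patient and/or cluster baseline characteristics (for example, age, gender, co-morbidities, educational level" and ends "marital status, proportion of COPD patients) in both the telehealthcare group and in the usual care group will be made". Adjustment is therefore conditional, is aimed at differences between the arms, and carries an illustrative list.

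Baseline SF-36 is available. Under Recruitment, the questionnaire covers "patients’ baseline health-related quality of life (EQ5D and SF-36) and demographic characteristics", and it must be returned before randomisation. The Recruitment and Randomization sections also say that the 26 districts are matched into 13 pairs and drawn pair by pair. The matching uses district population, estimated COPD prevalence and unemployment, not SF-36.

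**The concern.** Baseline SF-36 is likely to be the best single predictor of SF-36 a year later. A change score uses it with a fixed coefficient of 1, whereas regression on baseline estimates the coefficient, which is below 1 when scores regress to the mean. If one arm starts higher by chance, the change score over-corrects. With only 26 randomised units, chance imbalance is larger than 1,200 individually randomised patients would show.

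The second issue is the conditional rule. If covariates enter only when baseline differences look large enough, and no criterion is given, the primary model depends on the data. Nothing in the section requires the decision to be made before outcomes are known. The result is meant to inform a national decision on telehealthcare, so the primary estimate should come from one model chosen in advance.

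**Working it through.** **Inputs from the article.** Sample size section: SD 10, mean cluster size 50, coefficient of variation (CV) 0.5, ICC 0.05, target difference 5, 80% power, 350 per arm with at least seven clusters, 10% loss, about 800 in total. Elsewhere: 26 districts in 13 pairs, 1,200 patients expected. **Assumed:** rho, which the article does not give. The main range is 0.5 to 0.8.

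**1. The article's own figure.** Individually randomised n per arm = 2 × (10 × 2.8016 / 5)² = 62.8. Design effect = 1 + ((1 + 0.5²) × 50 − 1) × 0.05 = 4.075. The product is 255.9 per arm, or 5.12 clusters of 50. With a t reference, power is 0.780 at six clusters per arm and 0.852 at seven. Seven clusters of 50 give 350 per arm, and 700 / 0.9 = 778, close to 800. The stated size reproduces. SD 10 is a cross-sectional baseline SD. The SD of change is 10 × √(2(1 − rho)), which equals 10 only at rho = 0.5.

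**2. Chance baseline imbalance, pairing ignored.** Mean cluster size = 1,200 / 26 = 46.2. Design effect = 1 + (1.25 × 46.15 − 1) × 0.05 = 3.83. SE of the baseline difference = √(2 × 100 × 3.83 / 600) = 1.13 points. With 1,080 completers it is 1.15.

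**3. Error given that imbalance.** The change-score error is (rho − 1) × imbalance. Absolute size in points:

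| rho (assumed) | at 1 SE | at 1.96 SE |
|---|---|---|
| 0.5 | 0.57 | 1.11 |
| 0.7 | 0.34 | 0.66 |
| 0.8 | 0.23 | 0.44 |

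A simulation with 26 clusters, ICC 0.05 and CV 0.5 gave slopes of the change contrast on the imbalance of −0.51, −0.31 and −0.19 at rho 0.5, 0.7 and 0.8. For ANCOVA the slopes were about 0. The mean error of both estimators was about 0.

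**4. Precision, equal correlations at both levels.** Variance is proportional to 2(1 − rho) for change and 1 − rho² for ANCOVA, so the ratio is (1 + rho) / 2. This is 0.75, 0.85 and 0.90 at rho 0.5, 0.7 and 0.8 (simulated: 0.75, 0.84, 0.91). The avoidable variance is 25%, 15% and 10%.

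**5. Precision, cluster-level correlation higher.** For equal clusters of 46.15, a district mean has variance V = 100 × (0.05 + 0.95 / 46.15) = 7.06. The covariance of its baseline and follow-up values is C = 100 × (0.05 × rho_cluster + 0.95 × rho_individual / 46.15). Take 0.9 and 0.5: C = 5.53.
- Change: 2(V − C) = 3.06.
- Individual baseline only, slope 0.5: V(1 + 0.25) − C = 3.29, ratio 1.08.
- District-mean baseline added: V − C²/V = 2.73, ratio 0.89.

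With 0.9 and 0.7 (C = 5.94), the ratios are 0.98 and 0.92. Simulation of individual-level adjustment gave 1.07 and 0.97, with residual slopes on the imbalance of +0.27 and +0.13. Individual-level adjustment alone may therefore gain nothing, but adding the district mean restores a gain.

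**6. Power.** With 13 clusters per arm, 1,080 completers and 24 degrees of freedom, power for 5 points at rho 0.3 is 0.943 for change and 0.992 for ANCOVA. Both are higher at larger rho.

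**The case against.** The strongest reply is that this is a journal article and that exact model terms belong in an analysis plan. The covariate list and the multilevel model are both only examples. A change outcome with baseline as a covariate gives the same treatment estimate as ANCOVA, so the text does not rule out the better model. All of this is true. It does not settle the point, because the article states a rule: adjust if appropriate, for differences. A plan that fixed the model would have to replace that rule, not just fill in detail. The article nowhere commits to baseline SF-36 as a covariate.

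Three stronger readings are tempting, and the article supports none of them.
- *The primary estimate is biased.* It is not. Over randomisations the change contrast is unbiased, and the error arises only conditionally on a chance imbalance.
- *Baseline SF-36 is excluded.* It is unnamed in an open list, and it already enters through the change score.
- *The trial is underpowered as a result.* Power for 5 points stays at 0.94 or more with either analysis, even at rho 0.3.

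Two further limits stand. The SE of 1.13 ignores pairing and is too large to the extent that the matching variables track SF-36. The variance saving depends on an assumed rho and on how the correlation differs between levels.

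**Conclusion.** The point holds as one of efficiency, conditional accuracy and pre-specification. At a typical (one-SE) imbalance the change-score contrast is off by about 0.2 to 0.6 points for rho 0.8 to 0.5, against a 5-point target. The 1.1-point figure needs a 1.96-SE imbalance and the lowest rho together. Between 10 and 25% of the variance is avoidable if the two correlations are similar. If the cluster-level correlation is much higher, the saving is smaller, and it is absent for individual-level adjustment alone. The firmest part needs no assumed figure: adjustment tied to observed differences, with no criterion, leaves the primary model open to choice after the data are seen. The planned conclusion about a 5-point effect is not at risk.

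**What to change.** Replace the conditional adjustment sentence with a model fixed before randomisation: 12-month PCS on arm, baseline PCS (each patient's value and the district mean), randomisation pair and a district random effect. PCS is named here because the sample size rests on it. List any further covariates in advance and apply them whatever imbalance is observed. Report the unadjusted change contrast as a sensitivity analysis.

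No new data are needed, since baseline SF-36 is already collected and the pairs are known. Recruitment was ongoing at publication and randomisation follows baseline collection, so on the article's timetable the model could be fixed before allocation.

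The cost is a little more analysis work and some degrees of freedom. As fixed effects, the pairs use 12 and the district mean 1, leaving 26 − 1 − 1 − 12 − 1 = 11 instead of 24. The two-sided 5% t value rises from 2.06 to 2.20, about 7%. That can offset the roughly 5% fall in SE at rho 0.8 (√0.90 = 0.95) unless the pairs explain variance. At rho 0.5 the fall is about 13% (√0.75 = 0.87). Whether pair enters as a fixed or a random effect should therefore also be stated in advance.
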